## Goals and hypotheses

The primary objective of the study is to evaluate the effectiveness and cost-effectiveness of a culturally adapted SH + intervention combined with ECAU among university students in Indonesia at a three-month follow-up (main time point) in reducing psychological distress. The secondary objectives are to assess depression and anxiety symptoms separately, as well as perceived stress, functioning, quality of life, resilience, identified problems, feasibility, and acceptability. In addition, moderator variables influencing the reduction in psychological distress, anxiety, and depression symptoms and improvements in functioning and quality of life will be explored.

Previous research on SH + among South Sudanese female refugees in Uganda found that SH + reduced psychological distress three months after the intervention [22]. In addition, a follow-up period of three months is long enough to observe the sustained effects of the intervention while minimizing loss to follow-up and recall bias. In the context of our university student population, a three-month timeframe also aligns with academic terms, thereby reducing the risk of attrition due to changes in academic circumstances or different types of activities. For example, some students may have to enrol in an internship programme or live in a rural community for a full semester. Therefore, we expect that SH + with ECAU (SH+/ECAU) will be superior to the ECAU only in reducing psychological distress (primary outcome) at three-month follow-up, as well as the secondary outcomes of depression and anxiety, perceived stress, improved functioning, quality of life, resilience, and identified problems. Furthermore, we expect that SH+/ ECAU will report lower healthcare costs than ECAU-only.

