The Psychological Outcome Profiles instrument (PSYCHLOPS) assesses self-identified problems [50]. The PSYCHLOPS consists of four questions that cover three domains: problems (two questions), and functioning (one question), and wellbeing (one question). The participants are asked to give free answers to the problem and the functional domain. Responses are scored on a six-point scale, with producing a maximum score of 20. The pre- and post-therapy versions of PSYCHLOPS have the same four questions with additional in the post-therapy version about overall evaluation questions, a self-rated outcome ranging from ‘much better’ to ‘much worse’.

The Client Service Receipt Inventory (CSRI) [51] will be used to examine cost-effectiveness and health service utilization over the eight months (t1, t2, t3, t4). The questionnaire consists of questions concerning what kind of health services (public, private, university, or others), number of visits, type (in-person/ online), duration of contact, travel and waiting time, and travel cost. Additionally, trial costs will be collected (e.g. training, book printing, supervision).

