A health economic analysis will be conducted to assess the cost-effectiveness of SH+/ECAU compared with ECAU only, from both a health system and a societal perspective. The results of this analysis will be expressed as incremental cost-effectiveness ratios (ICERs) per quality-adjusted life years (QALYs) gained and per change in the PHQ-ADS composite score at the *t*_*3*_ follow-up assessment point (3 months). QALYs will be estimated using the EQ-5D-5 L questionnaire adapted to the Indonesian value set [46]. A deterministic sensitivity analysis will be performed to identify the most sensitive parameters affecting the ICER. The cost-effectiveness thresholds will follow the current guidelines for Indonesia, which is 1–3 times GDP per capita. The difference and QALY difference between the two groups will be estimated using generalized linear regression. The skewed distribution of the cost data was accounted for by estimating robust standard errors using the Huber-White sandwich estimator.

**Qualitative data (process evaluation). The** Interviews and FGDs will be audio recorded and transcribed verbatim. Thematic analysis will be carried out using ATLAS.ti [56].

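### The ICER is read against 1–3 times GDP per capita with only a deterministic uncertainty analysis named for it, and the protocol gives two different horizons for cost-effectiveness

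*Protocol article*

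**What the plan says.** Goals and hypotheses puts effectiveness and cost-effectiveness together in the primary objective, at the three-month follow-up.

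The health economic paragraph of Data analysis plans ICERs per QALY and per change in PHQ-ADS, reported at t3 (3 months). On estimation it says: "The difference and QALY difference between the two groups will be estimated using generalized linear regression". I read the first term as the cost difference. On skewness: "The skewed distribution of the cost data was accounted for by estimating robust standard errors using the Huber-White sandwich estimator". For the ratio it adds: "A deterministic sensitivity analysis will be performed to identify the most sensitive parameters affecting the ICER". The decision rule is: "The cost-effectiveness thresholds will follow the current guidelines for Indonesia, which is 1–3 times GDP per capita".

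Under Secondary outcome measure, the CSRI "will be used to examine cost-effectiveness and health service utilization over the eight months", with t1, t2, t3 and t4 listed. Table 1 schedules both the CSRI and the EQ-5D-5L at all four of these time points.

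**The concern.** The economic question is whether the ICER falls below a threshold, and the threshold range itself spans a factor of three. Answering it requires the sampling uncertainty of the ratio, or equivalently the probability that SH+ is cost-effective at a given threshold. A deterministic analysis moves one input or a few inputs and shows how the point estimate responds. It says nothing about how far the estimate would move in another sample of students. Robust standard errors describe a regression difference in one component. They give no interval for a ratio and do not contain the covariance between costs and QALYs. The reader would be left with a point ICER and no statement of how firmly it lies on either side of the threshold.

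The second problem is the horizon. One section ties cost-effectiveness to eight months, and two others to the three-month follow-up. Unless the protocol fixes one horizon, the choice can be made after the results are known, and costs and effects could be cut at different times.

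**Working it through.** **1. The two horizons.** t2 is at week 7, and t3 and t4 are 3 and 6 months after SH+. Counting from week 7, with 30.4375 days per month:

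- 7 × 7 / 30.4375 = 1.61 months
- t1 to t4: 1.61 + 6 = 7.6 months, which reproduces the stated eight months
- t1 to t3: 1.61 + 3 = 4.6 months

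The sections therefore differ by three months of follow-up. Since the CSRI and the EQ-5D-5L are both scheduled at t3 and t4, either horizon is feasible for both costs and QALYs.

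**2. What the component standard errors leave out.** With incremental cost ΔC, incremental QALYs ΔQ and threshold λ, net benefit is λΔQ − ΔC, and its variance is λ²Var(ΔQ) + Var(ΔC) − 2λCov(ΔQ, ΔC). Component standard errors supply the first two terms only. If the two components have equal SDs on the money scale (an assumption), the true SE is √(1 − r) times the value under independence:

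- r = −0.5: √1.5 = 1.22
- r = +0.5: √0.5 = 0.71

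**3. How imprecise the QALY denominator could be.** The documents give no utility gain or SD, so these are assumptions: a gain of 0.05 held over the whole period, and an SD of 0.10 or 0.20. The protocol's Sample size section gives 148 per arm, or 74 after its 50% attrition. Here the period is taken from the end of SH+ at about week 6, so t3 is at about week 19 and T = 19/52 = 0.365 year. Counting from week 7 gives 4.6/12 = 0.384, which scales gain and SE alike and does not alter which intervals include zero.

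QALY difference = 0.05 × 0.365 = 0.0183; SE = SD × 0.365 × √(2/n); 95% CI = difference ± 1.96 × SE.

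| SD | n per arm | SE | 95% CI |
|---|---|---|---|
| 0.20 | 74 | 0.0120 | −0.0053 to 0.0418 |
| 0.20 | 148 | 0.0085 | 0.0016 to 0.0349 |
| 0.10 | 74 | 0.0060 | 0.0065 to 0.0300 |

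With the incremental cost held fixed, the upper and lower limits differ by a factor of about 22 in the second row (0.0349/0.0016) and 4.6 in the third (0.0300/0.0065). Both exceed the threefold threshold range. Multiplying the SD by T assumes that utility is perfectly correlated over time. A lower correlation would narrow the intervals.

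**4. Baseline utility.** With the same SDs, a chance imbalance at t1 has SE = SD × √(2/n): 0.012 to 0.023 with 148 per arm and 0.016 to 0.033 with 74. If half to all of it persists to t3, it carries from 0.5 × 0.0116 × 0.365 = 0.002 to 0.0329 × 0.365 = 0.012 QALY (0.013 at T = 0.384), beside an assumed effect of 0.018.

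**The case against.** The article does not ignore sampling error altogether. It plans robust standard errors for skewed participant-level costs. It also gives the deterministic analysis a limited purpose, finding influential inputs, and does not say that nothing else will be done. A condensed article may leave bootstrap planes and acceptability curves to a full analysis plan. This has some force. It limits the point to the fact that the only uncertainty analysis named for the ratio does not answer the question set by the threshold. But the paragraph does specify the regression, the standard errors, the sensitivity analysis and the decision rule, so a mismatch among them is a fair comment on what is written.

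Three stronger readings are tempting, and the documents do not support them.

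- *Eight-month costs will be divided by a three-month effect.* No section says so. Because the CSRI is collected at each time point, costs can be cut at t3, and Data analysis can be read as placing the whole ICER there.
- *Costs and QALYs are modelled separately and without baseline utility.* The text does not say whether the models are fitted jointly or which covariates they contain. That is silence, and detail an article may omit.
- *The ICER interval will be unbounded.* That follows from one set of assumed inputs. With 148 per arm, or with SD 0.10, the QALY interval excludes zero. The 74 per arm also assumes complete cases, although multiple imputation is planned at three months.

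On importance, Goals and hypotheses includes cost-effectiveness in the primary objective, but the Abstract lists it among secondary outcomes, and Data analysis rests the main conclusion on the PHQ-ADS.

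**Conclusion.** The point holds in two parts. First, no method named for the ICER conveys its sampling uncertainty or the probability of cost-effectiveness across 1–3 times GDP per capita. Second, the CSRI description gives cost-effectiveness a horizon of about 7.6 months from baseline, while Goals and hypotheses and Data analysis give about 4.6 months, and these passages must be reconciled.

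The conflict of horizons rests on the protocol's own schedule. The size of the uncertainty rests on assumed utility gains and SDs. In all three illustrations the QALY interval is too wide for a point ICER to be judged against a threefold threshold range, but only one of them includes zero. Baseline adjustment is an improvement to the plan and not the correction of an error. The point affects the economic conclusion and leaves the PHQ-ADS comparison untouched.

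**What to change.** - State one common horizon for costs and effects in all three sections. For example, take t1–t3 as the base case, in line with Goals and hypotheses and Data analysis, and t1–t4 as a second analysis.
- Add a non-parametric bootstrap that resamples participants' cost–QALY pairs within arm, so that the correlation is kept. Report the cost-effectiveness plane and an acceptability curve, or net benefit, across 1–3 times GDP per capita. Resampling whole SH+ session groups is not advised: 148 participants in groups of 20–30 make only about 5 to 7 groups (148/30 = 4.9; 148/20 = 7.4), too few for a dependable cluster bootstrap.
- Include the EQ-5D-5L utility at t1 as a covariate in the QALY regression.
- Keep the deterministic analysis for unit costs and similar inputs.

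No new data are needed. The cost is additional analysis work, including combining the bootstrap with the planned multiple imputation, and an economic conclusion that may be less definite.

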#### Data management and confidentiality

The data collected by Castor EDC is automatically anonymized, and each participant will be assigned a unique participant number. The recording of the SH + session will be deleted as soon as it is checked with the fidelity checklist. The recording from the evaluation process, which consists of the interviews and the FGDs, will be deleted after the transcription of the recording is complete. The data management plan of this research can be accessed on https://dmponline.dcc.ac.uk/public_plans.

### Trial monitoring and adverse events reporting

(Serious) adverse events ((S)AEs) are defined as any undesirable experience that a participant has during the study, regardless of whether it is related to the study procedure or the SH + program. All SAEs will be recorded in Castor EDC and reported to the Research Ethics Committee of Universitas Padjadjaran. The research team will follow up with all SAEs until they are stabilized or resolved. If necessary, participants will be referred to a general practitioner. Participants may withdraw from the study at any time. No withdrawal criteria are specified.

To support participants who may require additional mental health care, we collaborate with the University Counselling Centre and have established a referral procedure. In this study, the research assistants have been trained to familiar with the mental health facilities available and know how to refer participants to the University Counselling Centre.

This study involves several potential risks, including emotional distress triggered during sessions and, in some cases, suicidal thoughts. To mitigate these risks, we have implemented a clear referral protocol for participants who express suicidal thoughts or severe distress. Facilitators are trained to respond sensitively and involve mental health professionals when necessary. Participants are informed of these procedures during the consent process and reminded that they can withdraw at any time without consequence.

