#### Enhanced care as usual (ECAU)

Enhanced care as usual (ECAU) consists of an e-leaflet containing information about support services at the university. This includes options for individual counselling and peer counselling and instructions on how to schedule an appointment. Other information includes mental health services outside universities and emergency contact for mental health issues.

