#### Facilitators

SH + will be delivered by two facilitators (a pair), and each university will have two to four facilitators. SH + facilitators have at least a bachelor’s degree in psychology. Individuals with a bachelor’s degree in psychology and who are currently in training to become a psychologist can be a facilitator.

There will be open recruitment to become a facilitator, and recruitment will start during the preparation of the study and before the recruitment of the study participants. The facilitator will receive up to 40 h of training based on the SH + training manual [54], and the total number of hours will depend on the skills and experience of the facilitators already has. The training will be conducted by the coordinator of this study (DA) or a clinical psychologist who has been trained by the coordinator of this study. The training will consist of basic helping skills, SH + facilitating skills, and managing participants’ distress, explaining the aims and background of the SH + intervention.

In addition to delivering SH+, the facilitator will be the one to contact participants to inform them of their randomization allocation. The facilitator will deliver the ECAU (i.e., leaflet) to all participants via email or media communication of the participant’s choice.

The clinical supervisor and facilitator will receive remote support and supervision from the research coordinator as needed. The facilitator will have an online group meeting with the supervisor who is a clinical psychologist to discuss protocol adherence, review barriers or potential barriers, facilitator concerns, any adverse effects and serious adverse events.

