## Abbreviations

ACT: Acceptance commitment therapy
CONSORT: Consolidated standard of reporting trials
CSRI: Client service receipt inventory
DWM: Doing what matters in times of stress
(S)AEs: Serious adverse events
ECAU: Enhanced care as usual
EDC: Electronic data capture
EQ-5D-5L: EuroQol 5-dimensional descriptive system—5-level version
GAD-7: Generalized Anxiety Disorder, seven-item measurement instrument
ICF: Informed consent form
ITT: Intention-to-treat
MIMIS: Mainz Inventory of Microstressors
PHQ-9: Patient Health Questionnaire depression module, 9-item measurement instrument
PP: Per protocol
SH+: Self-Help Plus
SPIRIT: Standard protocol items: recommendations for interventional trials
Unpad: Universitas Padjadjaran
WHO: World Health Organization
WHODAS 2.0: WHO Disability Assessment Schedule 2.0

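### Adverse events and serious adverse events share one definition with no seriousness criterion, yet recording, reporting and follow-up apply only to the serious ones; the only named source of event information also sees far more of the SH+ arm

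*Protocol article*

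**What the plan says.** Under Trial monitoring and adverse events reporting, the article introduces the two categories together: they "are defined as any undesirable experience that a participant has during the study, regardless of whether it is related to the study procedure or the" intervention. It gives no further definition of a serious event. The Abbreviations list does not separate the terms either, since its entry reads "S)AEs: Serious adverse events".

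The same section then states the duties:

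- Recording and reporting: "All SAEs will be recorded in Castor EDC and reported to the Research Ethics Committee of Universitas Padjadjaran".
- Follow-up: "The research team will follow up with all SAEs until they are stabilized or resolved".

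No recording rule is given for an event that is adverse but not serious.

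On how events come to light, the Facilitators section says that facilitators and their supervisor meet online to discuss protocol adherence and to "review barriers or potential barriers, facilitator concerns, any adverse effects and serious adverse events". The Self-Help Plus section gives facilitators five weekly sessions of 90–100 minutes with SH+ participants. For the control arm, "Enhanced care as usual (ECAU) consists of an e-leaflet containing information about support services at the university"; the facilitator contacts participants about their allocation and sends the leaflet.

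**The concern.** A reporting rule works only if staff can tell which events it covers. Here the rule selects SAEs, but the definition makes SAEs the same set as AEs. Two people applying the text in good faith could send the committee very different lists, and nothing in the article would show which list was right.

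The second matter is who hears about events. If they surface mainly through facilitators, the chance that an event is noticed depends on the arm. A table of events by arm, which a trial report would normally carry even without a formal test, would then mix true differences with differences in observation.

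**Working it through.** The article states no figure on this point, so the check is mainly a comparison of the text with itself.

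**Step 1. Does the definition support the duties?**

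| Element | What the article gives |
|---|---|
| AE | Any undesirable experience during the study, related or not |
| SAE | The same words |
| Seriousness criterion | None |
| Recorded in Castor | SAEs |
| Reported to the ethics committee | SAEs |
| Followed until stable or resolved | SAEs |
| Rule for non-serious AEs | None |

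Only two readings are available. If the definition is taken at its word, every AE is an SAE, and all three duties apply to every undesirable experience of 296 distressed students. If serious is meant to narrow the set, the narrowing rests on unstated judgement, and events judged non-serious have no recording rule. Neither reading gives a reproducible boundary.

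**Step 2. How much contact does the named source have with each arm?**

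- SH+: allocation notice, leaflet, and five weekly sessions.
- ECAU: allocation notice and leaflet; no later facilitator contact is described.
- Both arms: e-mailed self-report questionnaires at t1 to t4, with up to three reminders. Table 1 lists no adverse-event item.
- Research assistants: their described direct contact with participants is in recruitment and at screening. Their role in the safety section is referral.

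Facilitator contact after allocation is thus five sessions against none described.

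**Step 3. What could unequal detection do? (Illustration only.)** The arm size n = 148 is from the Sample size section. The true risk p, equal in both arms, and the detection rates s1 (SH+) and s0 (ECAU) are assumptions; the article gives none of them.

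Expected recorded events per arm = n × p × s. At p = 10%:

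- SH+, s1 = 90%: 148 × 0.10 × 0.90 = 13.3
- ECAU, s0 = 60%: 148 × 0.10 × 0.60 = 8.9
- ECAU, s0 = 30%: 148 × 0.10 × 0.30 = 4.4

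The apparent risk ratio is s1/s0, that is 0.90/0.60 = 1.5 or 0.90/0.30 = 3.0, with no true difference.

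The chance of a nominally significant excess in SH+ (two-sided 5% test of two proportions, normal approximation) is Φ[(d − 1.96 × SE0)/SE1]. Here d = p × s1 − p × s0, and SE0 and SE1 are the pooled and unpooled standard errors. For p = 10% and s0 = 30%: d = 0.09 − 0.03 = 0.06, SE0 = √(2 × 0.06 × 0.94/148) = 0.0276, SE1 = √((0.09 × 0.91 + 0.03 × 0.97)/148) = 0.0274. This gives Φ(0.21), about 59%. The range is:

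| True risk, both arms | s0 = 90% | s0 = 60% | s0 = 30% |
|---|---|---|---|
| 5% | 2.5% | 10% | 33% |
| 10% | 2.5% | 16% | 59% |
| 20% | 2.5% | 30% | 89% |

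The table shows that the result depends almost wholly on detection rates that nobody knows. It does not show that the bias exists in this trial.

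**The case against.** The strongest reply is that this is a condensed article. How events are elicited may be set out in the full protocol, and silence on that is no fault. This stands for elicitation. It does not cover the definition, because the article does state one and attaches duties that it cannot support.

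A reader might also infer more than the text supports:

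- **That a between-arm harms comparison is invalidated.** No such comparison is planned. Harms are not among the listed outcomes and the Data analysis section does not mention them. The scale-up statement in the Abstract is conditional on effectiveness and makes no safety claim.
- **That facilitators are the only route of detection.** The Facilitators section describes a supervision meeting, not a collection method. The safety section gives the research team follow-up of all SAEs and the research assistants a referral role. It also describes a referral protocol for participants who express suicidal thoughts or severe distress. None of these is limited to SH+. Facilitators are the only named source, which is a weaker statement.
- **That harm in ECAU, or after week 7, goes unseen.** Both arms complete PHQ-9, GAD-7, PSS, WHODAS 2.0 and the CSRI at t2, t3 and t4, so worsening of symptoms or functioning and use of services are measured alike.
- **That Table 1 proves there is no adverse-event item.** Table 1 is not exhaustive: it also omits the Suicide Ideation Scale and the contamination questions. The missing row is weak evidence.
- **That SH+ will show more events.** It may. The direction is plausible from the contact pattern, but the article gives nothing from which to estimate the size or establish the existence of a bias.

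**Conclusion.** The definitional fault is established from the text alone and needs no assumption: AEs and SAEs are one class by definition and two classes by duty. This alone warrants correction.

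The ascertainment point holds in a limited form. The only named source of event information has much more contact with SH+ than with ECAU, so any tabulation of events by arm would be open to bias of unknown size. That rests on events surfacing largely through facilitators and on no equal elicitation being specified elsewhere; the article neither confirms nor excludes either. The primary outcome and its analysis are unaffected.

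**What to change.** 1. Keep the present wording as the definition of an AE. Add a separate definition of an SAE with explicit seriousness criteria, and correct the abbreviation entry to match.
2. State that non-serious AEs are also recorded in Castor.
3. Add one identical adverse-event question to the t2, t3 and t4 questionnaires in both arms, and use it for any tabulation of AEs by arm.
4. Continue to report all SAEs from any source by arm, with the source stated. List facilitator-reported events separately. The questionnaire item should not be the sole basis for SAEs: the trial plans for 50% attrition, and people with serious events may be among those who do not reply.

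The cost is a few lines of text, one short item in questionnaires that already go to both arms, and staff time to review and act on the replies. The article reports that the trial had not started as of December 2024, with first inclusion expected in March 2025. If inclusion has since begun, the date of the change should be recorded and the item introduced in both arms at once.
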